## Abstract

**Background:**

The inclusion of fathers’ participation during the perinatal period is an important strategy for improving mothers’ health. No studies have yet been conducted in Iran to explain the concept, obstacles and facilitators of fathers’ participation during the perinatal period. Thus, this study will be carried out to provide a comprehensive interventional program for promoting fathers’ participation in the perinatal care.

**Methods:**

This study is a sequential exploratory (qualitative – quantitative) mixed methods design that consists of three consecutive phases. In this study, following a qualitative approach, the researchers will explain the concept, obstacles, facilitators and strategies related to promoting fathers’ participation in perinatal care. In the second phase, researchers will design an appropriate and comprehensive interventional program for promoting fathers’ participation in perinatal care by using the results of the qualitative phase and literature reviews. The proposed interventional program is designed by a panel of experts based on prioritization guidelines and will be finalized for execution. In the third stage, the effectiveness of interventional program on the awareness, attitude and practice of fathers about participation in perinatal care will be investigated in a semi-experimental study.

**Discussion:**

It is expected that from the results of the present mixed methods study, by presenting an interventional culturally sensitive program which is appropriate for the conditions of the society for expectant fathers, the participation of fathers in the perinatal period will increase and thus lead to improvements in the health of the mother and the infant. If this interventional program is effective, it could be included in the perinatal health care guidelines.

**Trial registration:**

IRCT20160224026756N4 Registered 27 May 2018.

## Plain English summary

Fathers’ participation during the perinatal period is an important strategy for improving mothers’ health**.** The results of this study offer a rich source of information for the required interventions to promote the health of the mothers and infants during pregnancy and postpartum period. This study is a sequential exploratory (qualitative – quantitative) mixed methods design that consists of three consecutive phases. In this study, following a qualitative approach, the researchers will explain the concept, obstacles, facilitators and strategies related to promoting fathers’ participation in perinatal care. In the second phase, the researcher will design an appropriate interventional program for promoting fathers’ participation in perinatal care by using the results of the qualitative phase and literature reviews. The purposed interventional program is designed by a panel of experts based on prioritization guidelines and will be finalized for execution. In the third stage, the effectiveness of interventional program on the awareness, attitude and practice of fathers about participation in perinatal care will be investigated in a semi-experimental study. Therefore, it is expected that conducting a mixed method study by presenting an interventional culturally sensitive program which is appropriate for the conditions of the society for expectant fathers, the participation of fathers in the perinatal period will increase and thus, improve the health of the mother and the infant.

## Background

Throughout life, special stages which would leave a profound impact on individual’s life exist [1]. One of these stages is pregnancy and delivery, which is the greatest event in a woman’s life and her family. According to the 7th clinical guideline of the American College of Obstetricians and Gynecologists, and the American Academy of Pediatrics in 2012, perinatal care include a full range of preconception counseling, preparing prenatal and delivery care, neonatal care and postpartum care [2] and the main goal of these care is to prevent any complications for the mother and the infant [3]. Men’s participation is an important strategy for reaching the third Millennium Development Goals (MDGs) such as women’s empowerment and improvement of mothers’ health [4]. Many studies have mentioned the positive outcomes of men’s participation during pregnancy and delivery [5–8]. In this regard, in the International Conference on Population and Development (ICPD) in 1994, the shared responsibility of men and improvement of their active participation in parental responsibilities, sexual behaviors and reproductive responsibility in family planning, pregnancy health, maternal-neonatal health, preventing unwanted and risky pregnancies, health and nutrition of the children and preventing violence against women and children, were emphasized [9]. But despite this emphasis and international agreement on the importance of men’s participation for the improvement of maternal and neonatal health, advancements in this regard are slow and there are challenges in preparing the environments for the presence and participation of men in the care of mothers [10], in a way that the United Nations Population Fund in 2009 stated that:“ Despite the significant evidence about the benefits of men’s participation thus far, and although men have responded well to the efforts of their participation during delivery., their participation during pregnancy, delivery and childcare has not been effectively promoted globally” [9].

No specific formula exists for men’s participation in the healthcare system and the most accepted strategies are those that are culturally acceptable, appropriate and applicable. To find these strategies, research and need-assessment should be conducted [11]. In this regard, during the recent years in industrial Western countries, fathers’ participation and presence during pregnancy and delivery has been increased [12]; but in most parts of the world, men’s participation is the missing link in countries’ and governments’ policies, information and plans and it is usually neglected and most of the global health systems have no specific plan for attracting men’s participation in reproductive health programs [13]. In Iran, like many other countries, the governmental departments have considered the usual care for women, but no comprehensive plan exists for men. Only during recent years, for encouraging women to have vaginal delivery, delivery preparation classes are being conducted for pregnant women in 8 sessions and the husband can participate in one session. But practically, this matter is just being executed at a limited number of health centers and there are problems for executing this program. Also, in some hospitals, fathers who have participated in the delivery preparation classes are allowed to be with their wives during labor and delivery but this is also very limited. Furthermore, the paternity leave for fathers, which is a two-week leave, would only be given to men with working wives; but this could not be generalized for all of the male employees or even to those whose wives have a part-time job with no insurance policy [14]. However, this plan is still not being implemented by all the organizations and offices. So far, most of the conducted studies about men’s participation, internationally and nationally, were about family planning, sexually transmitted diseases (STD) and AIDS; while other aspects of women’s health like pregnancy and delivery were not considered much; even though the need for information in these fields is necessary [12].

Therefore, regarding the informational challenge about father’s role in mothers’ health and also due to the lack of a comprehensive program for father’s participation based on Iranian culture, this study will be carried out to provide a comprehensive and culturally sensitive program for father’s participation during the perinatal period.

### Objectives

The objectives of each phase are as follows:

#### Objectives of the first phase: qualitative study

To explain the concept, obstacles, facilitators and strategies of father’s participation in perinatal care.

#### Objectives of the second phase: program design

To design a preliminary interventional program based on the data extracted from the qualitative phase and the review of texts.

To validate the interventional program by a panel of experts.

#### Objectives of the third phase: quantitative study

To determine the effect of the designed interventional program on awareness, attitude and practice of fathers about participation in perinatal care.

## Methods/Design

This study is a sequential exploratory (qualitative – quantitative) mixed methods design that consists of three consecutive phases. In this study, following a qualitative approach, the researchers will explain the concept, obstacles, facilitators and strategies related to promoting father’s participation in perinatal care**.** In the second phase, the researcher will design an appropriate interventional program for promoting father’s participation in perinatal care by using the results of the qualitative phase and literature reviews (Fig. 1). The purposed intervention is designed by a panel of experts based on prioritization guidelines and will be finalized for execution. In the third stage, the effectiveness of interventional program on the awareness, attitude and practice of fathers on their participation in perinatal care will be investigated in a semi-experimental study.

**Fig. 1 Fig1:**
[figure not shown]
Study visual diagram

### Phase I: Qualitative study

At this phase, the researcher is trying to discover the concept and identification of barriers and strategies for father’s participation in the perinatal period to design an interventional program for their participation. This study is carried out using qualitative content analysis method.

#### Participants in the qualitative phase

Participants of this phase will be men whose wives are pregnant or have experienced delivery, pregnant or delivered women, midwives, gynecologists and nurses, and also managers at the level of health deputy of the Tabriz University of Medical Sciences, Iran as well as maternal health policy makers of the Ministry of Health and Medical Education.

#### Sampling method

In the qualitative phase of this study, the sampling will start purposively [15] and continue considering the maximum variety in educational level, socioeconomic condition, job, age, and number of pregnancies and deliveries (for the mothers group). Also, healthcare providers with different working experience and from different health centers as well as maternal health policy makers would be recruited for the study.

#### Inclusion criteria for men and women

The inclusion criteria are willingness to participate in the study, providing informed consent, being able to understand and express their experiences and having Iranian Nationality.

#### Inclusion criteria for care providers

Having at least 5 years of working experience and willingness to participate in the study.

#### Research environment

The interviews will be conducted at the time and place of the participants’ desire (hospitals, midwifery or gynecologists’ offices, prenatal clinics, universities, home, etc.).

#### Data collection process

After selecting each participant, the researcher will introduce herself and state the main objectives of the study in order to gain participant’s trust to ensure the confidentiality of the interviews. The researchers will ensure that the participants have their freedom to discontinue their cooperation with the study whenever they want. After obtaining a verbal and written consent from the participants, the interviews will be recorded using MP4 device. In case where sound recording is not allowed, interviews will be conducted by taking notes.

Data will be collected through in-depth interviews, focus group discussions and field notes. The interviews will begin with the open questions of “How men can participate in the care of their wives during pregnancy, delivery and after delivery? What are the men’s participation barriers in perinatal care and what are the men’s participation facilitators in perinatal care? Please explain.” And then the paths of the interviews will be guided through participants’ open and interpretative answers. Data gathering will continue until data saturation [16] and no new data code will emerge in the interviews.

#### Data analysis

Data will be analyzed using conventional content analysis [17]. At the first opportunity after recording the interviews, the researcher will regularly change the recordings into texts. Then the written texts will be reviewed repeatedly to achieve a comprehensive understanding of the interviews. Afterward, sentences and phrases will be coded and after creating the codes using inductive method; similar codes will be merged with each other and those with similar meanings will be put in the same categories to create the sub-categories. This will be done by constant comparison of all the data. Eventually, using inductive process, similar sub-categories will be merged into main categories.

#### Accuracy and reliability of qualitative data

To judge the correctness of the data, dependability, credibility, transferability and confirmability standards will be used [15]. To provide the credibility of the results, different methods including in-depth interviews at different times and places, a combination of data gathering methods such as individual interviews, focus group discussions and the maximum variation in selecting the participants will be used. Review by the participants will be used to confirm the accuracy of the data and extracted codes; also, experts’ opinions will be used to ensure that the results are compatible with participants’ opinions. In the present study, for increase transferability, the results will be given to people who did not participate in the study and had similar characteristics to the participants so that they would judge about the similarity of the results based on their own experiences.

### Phase II: Designing interventional program

After explaining the concept, barriers and facilitators of father’s participation in perinatal care and also determining the interventional strategies from the participants’ point of view in the qualitative study, the researcher will review related papers and texts. At this stage, the search and review of the relevant texts will be done to confirm and complete the interventional strategies taken in the qualitative phase of the study thereby designing an interventional program for father’s participation in perinatal care.

The method of review will be narrative review with searching in electronic and library resources including reference books and theses. Databases that will be used to search and identify related articles, are PubMed, Cochrane, Google, Google scholar, SID, Magiran, Iranmedx, Scopus, Science Direct, Uptodate, Springer, Biomed Central, WHO and UNFPA. All the studies published between 2005 and 2018, both in English and Persian languages with qualitative, quantitative, and mixed methods study and with the keywords: male involvement, men’s participation**,** fathers’ participation, fathers’ involvement, reproductive health, perinatal care, maternity care, perinatal period, maternal and newborn health, safe motherhood, safe delivery, barriers, intervention, interventional strategy, antenatal and postnatal care, prenatal care, pregnancy and childbirth, paternal support, program, postpartum care, will be reviewed. To perform the search, these keywords including And or Space Operators between different words and from Or to similar words will be used. The star’s mark will be used at the end of the phrase to find the exact phrase of the string and to search for all of the items.

#### Holding a panel of experts

At this stage, the drafting of the strategies extracted from the qualitative research and review of the text will be prioritized using the decision matrix. In this way, these strategies will be presented to a number of experts in the first Delphi round in terms of cost, ease of implementation, timing and effectiveness; and for each dimension, a score between 1 and 3 will be considered.

After completing the decision matrix by them and collecting comments, prioritizing of strategies based on the score given by each member will be done for each dimension of intervention and strategies related to each dimension. Then, an intervention program will be designed for the highest priority strategies and in the second round of Delphi, a preliminary version of the proposed intervention program will be designed, and will be presented and evaluated in panel discussion in the presence of the research team and experts (including reproductive health specialists, gynecologists, midwives and managers at the level of health deputy). A few days before the meeting, a copy of the proposed intervention program will be made available to the panel members to write their comments. Then, based on the panel members’ views, corrections will be made to the designed intervention program, and subsequently finalized and implemented in the quantitative phase (Phase III of the study).

### Phase III: Quantitative study

#### Type and direction of the quantitative study

The quantitative phase of the research will be implemented as a three-group semi-experimental study.

#### The studied population

In this study, the target population is all pregnant women with a gestational age of 20 to 22 weeks and whose husbands have referred to prenatal clinics affiliated to the Social Security Organization of Tabriz.

#### Research sample

The research sample will be formed from the study population who entered the study with convenience sampling and have the inclusion criteria.

#### Research environment

The research environment is three prenatal clinics which are affiliated to the Social Security Organization of Tabriz city. The reason for choosing such environment is the convenient access to pregnant women and their husbands in these settings and due to the fact that these centers have high daily attendance rates.

#### Sample size

The sample size calculation is based on the results of previous studies, based on knowledge, attitude and practice variables using G-power software. The maximum sample size based on the practice variable and considering the data [power 95%, two sided α = 0.05, sd_2_ = 6.34, m_2_ = 88.81, sd_1_ = 14.69, m_1_ = 76.18] will be calculated with 22 people in each group, and due to probability of 10% loss, total sample size will be considered as 24. The final sample size will be determined based on the pilot study.

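### The sample size section gives a total of 24 after allowing for loss, which cannot stand beside 22 per group in a three-group trial; 24 per group (72 in total) is the likely intent

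*Protocol article*

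**What the plan says.** In the protocol article, the Phase III section headed Sample size bases the calculation on the practice score, the outcome that needs the largest sample. It specifies 95% power, "two sided α = 0.05", and means and standard deviations from previous studies: "sd_1_ = 14.69, m_1_ = 76.18" for one group and "sd_2_ = 6.34, m_2_ = 88.81" for the other. It concludes that the number "will be calculated with 22 people in each group, and due to probability of 10% loss, total sample size will be considered as 24". The next sentence adds: "The final sample size will be determined based on the pilot study".

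The number of groups is given elsewhere. The section on the type and direction of the quantitative study says: "The quantitative phase of the research will be implemented as a three-group semi-experimental study". The Phase III section on sampling method confirms two intervention arms and one control arm, each drawn from a different clinic, and the section on the research environment lists three clinics.

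**The concern.** One sentence sets the requirement per group and then gives a total that is barely larger than a single group. With three groups the two figures cannot both be right. The size of the trial is a basic design figure. A reader who wants to know how many couples will be recruited finds no usable total, and the per-group and whole-trial readings of 24 differ threefold. A second, much smaller question is whether 24, taken as a per-group figure, covers the 10% loss it is meant to cover.

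**Working it through.** **Inputs.** All come from the Sample size section, except the number of groups (3), which comes from the sections on study type and sampling method. Means 76.18 and 88.81; SDs 14.69 and 6.34; two-sided α 0.05; power 95%; 22 per group; loss 10%; stated total 24. Equal group sizes are assumed, because the text speaks of the same number in each group.

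**Step 1: reproduce the 22.**
- Difference: 88.81 − 76.18 = 12.63.
- Root-mean-square SD: √((14.69² + 6.34²)/2) = √((215.80 + 40.20)/2) = 11.31.
- Standardised difference: d = 12.63/11.31 = 1.116.
- Power of the two-sample t-test, from the noncentral t distribution with noncentrality d·√(n/2) and 2n − 2 degrees of freedom: 94.2% at n = 21 and 95.1% at n = 22.

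The smallest n that reaches 95% is 22, so the stated per-group figure reproduces. (The normal approximation gives 21.) The fault lies only in the step from 22 to 24.

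**Step 2: test 24 as a total.**
- Before loss: 3 × 22 = 66. Even two groups would need 2 × 22 = 44.
- After 10% loss: 66/0.9 = 73.3, so 74 if the total is inflated. Per group, 22/0.9 = 24.4, so 25, and 3 × 25 = 75.
- A total of 24 therefore fails before loss is considered.
- Literal consequence: 24/3 = 8 per group, with power 54.7% before loss and 48.4% with 7 completers per group.

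**Step 3: test 24 as a per-group figure.**
- 22/0.9 = 24.4 and 22 × 1.1 = 24.2. Both fall just above 24, so 24 is what results if either is rounded down.
- Total: 3 × 24 = 72.
- After 10% loss: 24 × 0.9 = 21.6 per group, against 22 needed; overall 72 × 0.9 = 64.8, against 66.
- Power: 94.8% at the expected 21.6, or 94.2% if completers are rounded down to 21.
- With 25 per group: 25 × 0.9 = 22.5, so at least 22 after rounding down, and power 95.1%.

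| Reading of the 24 | Recruited per group | Total | Completers per group after 10% loss | Power, one two-group comparison |
|---|---|---|---|---|
| Whole trial (literal) | 8 | 24 | 7.2 | 48.4% at 7; 54.7% with no loss |
| Per group (likely intent) | 24 | 72 | 21.6 | 94.2% at 21; 94.8% at 21.6 |
| For comparison: 22/0.9 rounded up | 25 | 75 | 22.5 | 95.1% at 22 |

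**The case against.** The strongest reply is that this is a slip of one word. The sentence starts from 22 per group and raises it for loss; 24 follows naturally from 22 and cannot follow from 66. On that reading the design is adequate, and the rounding gap of under half a person per group is negligible beside a loss rate that is itself a round assumption. Most of this stands. It identifies the likely intent and sets the scale of the problem. It does not remove the contradiction, because the sentence calls 24 a total and nothing elsewhere corrects it. Nor is this a detail left out of a condensed article: two printed figures conflict.

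A reader might make two stronger inferences, and the documents support neither.

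- **That the trial will recruit only a third of what it needs.** This requires reading the 24 against the clause just before it. The 55% power is what the literal wording implies, not a forecast.
- **That the pilot could shrink the trial after a chance-large effect.** The article says only that the pilot will settle the final size. It does not say that a pilot effect will replace the planned difference or that the number may be lowered, and how the pilot is used may be set out in the full protocol. The pilot sentence matters here only in that it does not say whether 24 is a total or a per-group figure.

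**Conclusion.** The point holds as an error in a stated figure. A total of 24 is incompatible with 22 in each of three groups, which makes 66 before loss and 74 to 75 after it. The 22 per group is correct on its inputs, and 24 per group, 72 in total, is the likely intent. On that reading the allowance for loss is slightly short, by 0.4 of a person per group and under one percentage point of power. That is a rounding remark and would not merit a finding alone.

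This rests on equal groups, 10% loss in each, and the article's own means and SDs. The power figures apply to a single comparison of two groups. Whether such a calculation suits a three-group comparison with one clinic per group is a separate question, not judged here. The wording needs correcting because it misstates the size of the trial; the calculation of 22 does not need to be redone.

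**What to change.** In the Sample size section, replace the phrase that gives 24 as the total with one of these:

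- **24 per group, 72 in total (about 94% power for one two-group comparison after 10% loss).** This needs no couples beyond the likely intent; only the power statement changes.
- **25 per group, 75 in total**, if the stated 95% power is to be kept after loss. This adds 3 couples to the 72.

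Either way, state both the per-group number and the three-group total. The cost is one phrase and at most three more couples.
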